## Methods

### Study setting

The study is conducted within a Bachelor of Science Psychology program at a medium sized university in a medium sized German city. Most data will be collected using an online survey tool, EFS Survey developed by Tivian, and the online learning platform “Stud.IP” which is routinely used at the university.

### Study design

The study is a cluster-randomised controlled trial, with psychology students at a university enrolled in communication skill seminars. The rationale to adopt a cluster-randomised controlled trial design, increasingly used for educational research [18], is as follows: In the context of seminar-based communication training, students within a single class are likely to share resources, study materials, and informal peer discussions. Randomising at the individual level could lead to contamination, where participants assigned to different interventions (AI-based vs. conventional) might inadvertently share experiences. By implementing a cluster-level randomisation (i.e., randomising entire classes), we preserve ecological validity – each class follows a uniform teaching approach – and reduce risk of cross-condition interference [19]. This design choice is also practical for scheduling, teaching logistics, and ethical considerations, ensuring that all students in a class receive the same structured training. Based on practical constraints of the field study (e.g., differing semester schedules, teacher availability, or institutional requirements), classes will be assigned using a parallel group design (see Fig. 1).

**Fig. 1 Fig1:**
[figure not shown]
Study design. Notes: Classes follow a parallel group design (randomised to Clusters Type A vs. B: AI condition vs. TAU only). Cluster Type C represents optional, non-randomised classes that can serve as observational comparators and are not part of main analyses. Abbreviations: AI, artificial intelligence; CSS, communication skills seminar; TAU, taught as usual

In the parallel group design, classes are randomised to the AI condition (Cluster Type A, with Condition 1 only: AI-enhanced exercises alongside teaching-as-usual, TAU, that includes classical exercises) or the control condition (Cluster Type B, Condition 2: TAU only). Additional non-randomised comparison classes (Cluster Type C, Condition 3) will comprise students with TAU only but not be included in the main analyses.

Details regarding the Conditions are as follows:

In Condition 1 (Intervention with AI-enhanced exercises alongside TAU), Participants will use AI-enhanced communication skill exercises provided via the HAWKI platform alongside TAU, in the context of the standard communication skills seminar, which includes not-AI-enhanced communication skills exercises. HAWKI is a data protection-compliant platform that serves as a wrapper for OpenAI's ChatGPT. HAWKI is web-based and grants access to state-of-the-art language models (currently GPT-4o), made available through university accounts to protect personal log-in data. It thereby allows users to interact with ChatGPT without requiring personal account creation with OpenAI, thereby enhancing user privacy and aligning with General Data Protection Regulation (GDPR) standards. Students receive access to HAWKI and instructions for its use through the online learning platform ‘Stud.IP’. The exercises will involve AI-facilitated interactions designed to simulate real communication scenarios. Students will follow structured system prompts tailored to improve their communication skills. This condition will be implemented for the full duration of the seminar. The content of the intervention is described in more detail below.

During times where Condition 2 (first comparator, TAU only) is active, participants will attend the standard communication skills seminar, which includes not-AI-enhanced communication skills exercises. This condition will be implemented for the full duration of the seminar within the semester lecture period, with participants getting no specific access to AI tools or related prompts outlined in Condition 1.

Participants undergoing Condition 3 (second, non-randomised comparator, TAU only) will attend communication skills seminar with instructions and exercises comparable to those in Condition 2. This Condition will serve as an observational, non-randomised control to compare against condition 1, but not be part of the main analyses. It is added due to procedural reasons in cases where randomisation of a seminar to Conditions 1 or 2 is not feasible. This may occur for example if certain classes already began instruction before randomisation could take place or if they are run by instructors who cannot accommodate the required arrangement. Such classes serve as an additional, observational comparator to explore potential baseline or contextual differences. We will address these differences by adjusting for key covariates (e.g., baseline skill levels) in the analyses.

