**Methods:**

In this cluster-randomised controlled trial, psychology students enrolled in communication skill seminars at a medium sized university in a medium sized German city will participate. Classes will be assigned within a parallel group design to the AI condition (AI-enhanced exercises alongside teaching-as-usual, TAU, that includes classical exercises) or the control condition (TAU only). Additional non-randomised comparison classes will comprise students with TAU only, but not be part of main analyses. The primary outcome is the change in communication skills from baseline, assessed through questions reflecting the communication techniques emphasised in the training. Secondary outcomes include communication skills, self-efficacy and self-concept, motivation, attitudes toward AI, user experience with the AI tool, student evaluations of course quality, and feasibility aspects such as uptake and usability. Data will be collected via online surveys and the university’s teaching platform. Statistical analyses will employ mixed models to evaluate the intervention’s impact.

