### Description of AI-based communication skills exercise

The intervention component of this trial involves AI-enhanced communication skill exercises specifically designed to foster basic communication abilities using principles from motivational interviewing and other communication frameworks. The exercises utilise a set of system prompts developed to tailor the generative AI to interact with students as intended. Each exercise session begins with the AI mentioning or outlining the motivational interviewing technique, followed by a short vignette or task that students shall respond to by applying the respective or appropriate technique. After students submit their responses, the AI provides feedback based on predetermined criteria that reflect best practices in the respective technique. Students are also encouraged to tailor their interactions with the AI to simulate conversations with specific personas or subjects possessing distinct characteristics or communication needs. This includes the option for language practice beyond German, accommodating a wider range of communication scenarios. Participants are instructed not to provide any personal information within the interactions with the AI.

To facilitate a structured learning experience, students can request example answers from the system. This feature is intended to provide students with model solutions to compare against their responses. Students interact with these prompts through the HAWKI interface, which connects them to advanced language models from OpenAI’s GPT framework. After each set of interactions, students are required to document the exchange by copying the transcript of their conversation with the AI into a designated field on the Stud.IP platform, ensuring that their responses are recorded and assessable.

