*Contribution of Output to Clinical Practice and Decision-Making. *The output of the AI intervention is primarily educational and does not directly contribute to clinical decision-making. However, the intervention is designed to enhance the communication skills of psychology students, which is crucial in their professional training and future clinical interactions. By improving these skills, the AI intervention indirectly supports students in making informed decisions and effectively communicating in various future professional settings.

*User access.* Integration of the AI intervention necessitates setting up access to the HAWKI platform, either via devices provided by the university, or from offsite, where participants require a reliable internet connection to access the platform remotely.

*Human-AI Interaction and Required User Expertise.* Human-AI interaction is facilitated primarily through the setup and oversight of the AI operations. The system is designed to be user-friendly, requiring no specific technical expertise beyond proficiency with the online learning platform Stud.IP, which is routinely used in classes at the university. This approach ensures that all users, irrespective of their technical background, can efficiently engage with the AI without extensive training.

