*Abbreviations*: *AI* artificial intelligence, *ASC* academic self-concept, *SE-12* self-efficacy questionnaire, *SE-12 G* German self-efficacy questionnaire

^a^The nonrandomised control condition (Cluster Type C) completes the same measures as the control condition in the randomised Cluster Types

The primary outcome is the change in communication skills from baseline, measured using a set of questions designed to reflect the communication skills emphasised in the training. This outcome will be assessed at two time points: t0 (baseline, before the start of training phase) and t1 (end of seminar, after training phase). The primary outcome will be analysed as a z-standardised change score to evaluate the improvement from baseline to subsequent time points. We use data collected during a study pilot phase during winter-term 2024/25, to pilot the set of questions and adapt the assessment if necessary.

Secondary outcomes include measures related to the participants of the course, the use of AI and the perceived quality of the course, such as attitudes towards AI, self-concept and self-efficacy, motivation, user experience with the AI tool, as well as students’ evaluations and feedback. These outcomes are assessed at various time points throughout the course using a combination of validated scales and self-developed measures, as detailed in Table 1.

Each student’s interaction with the AI-system is recorded and can be analysed using criteria derived from motivational interviewing best practices (Motivational Interviewing Treatment Integrity, MITI, 4.2) [32] by human raters and AI. These assessments focus on the accuracy and appropriateness of the techniques used.

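### The plan states no safeguard against AI-assisted answering of the primary test at t1, when only the AI arm has been given the tool, its prompts and example answers

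*Protocol article*

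**What the plan says.** **Outcome and timing.** Study outcomes states: "The primary outcome is the change in communication skills from baseline, measured using a set of questions designed to reflect the communication skills emphasised in" (that is, in seminar training). The two time points are "t0 (baseline, before the start of training phase) and t1 (end of seminar, after training phase"). Table 1 lists the competence test at both time points in both arms, without a mode of administration. Allocation concealment/blinding says that raters who judge free-text responses are blinded to condition, which suggests that at least part of the test is free text.

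**Mode of collection.** The abstract says: "Data will be collected via online surveys and the university’s teaching platform". Study setting says: "Most data will be collected using an online survey tool". Data management repeats that most data come through the survey tool, but also mentions direct assessments without saying which measures these are. Data analyses relies on online collection to limit missing data.

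**Access to AI.** For Condition 1, Study design says: "This condition will be implemented for the full duration of the seminar". The description of the exercises adds tailored prompts, feedback against best-practice criteria, and that "students can request example answers from the system". HAWKI is web-based and can be used off campus, where "participants require a reliable internet connection to access the platform remotely". Condition 2 is described as "participants getting no specific access to AI tools or related prompts outlined in Condition 1".

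**The concern.** The trial asks whether practising with AI improves the student's own communication skill. That requires the t1 score to reflect what the student can do unaided. At t1 the AI arm has spent a term with a tool that is prompted for the tested techniques, can be reached from home and supplies model answers. The control arm has been given no such tool. If some AI-arm students consult it, or another AI tool, while answering, their scores rise for a reason other than learning.

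The planned methods do not remove this:

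- **Baseline adjustment.** At t0 neither arm has used the study prompts, so a difference that arises only at t1 goes straight into the change score.
- **Rater blinding.** It protects the scoring, but here the answer itself has changed.
- **ITT and per-protocol analyses.** Both use the same t1 scores.

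Nor can a later analysis recover the information if neither AI use nor the place of completion was recorded.

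**Working it through.** The plan gives no figure for AI use during the test, so there is nothing to reproduce. The check has two parts.

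**1. Do the sections together close the gap?**

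- *Is the test online?* Four places (abstract, Study setting, Data management, Data analyses) describe online collection. One phrase in Data management allows direct assessments. None names the primary test. Online is the likelier reading, but it is an inference.
- *Has access ended by t1?* Study outcomes puts t1 after the training phase. That fixes the order of events. It does not say that HAWKI or the prompts become unavailable.
- *Is AI use barred at the test?* The article contains no such instruction and describes no supervised sitting.
- *Do the arms differ?* They differ in what the study provides. They may not differ in actual use, since controls are not barred from public AI tools.

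**2. How large could the effect be?**

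Inputs:

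- p, the excess share of AI-arm students over controls who answer with AI at t1: assumed.
- g, the score gain per assisted test, in SDs of the analysed score: assumed.
- Medium effect: taken as 0.5 SD (assumed; the plan says only medium).
- 50 students per arm: from the sample size section.
- Alpha 0.05: from Data analyses; two-sided is assumed.

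Bias = p × g.

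Chance of a significant result with no true skill effect, by normal approximation: SE = √(2/50) = 0.20, and P = Φ(bias/SE − 1.96) + Φ(−bias/SE − 1.96). For the clustered version, the SE is multiplied by √1.45, where 1.45 = 1 + (10 − 1) × 0.05, assuming an ICC of 0.05 and 10 students per class.

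| p | g (SD) | Bias (SD) | Share of 0.5 SD | P, no clustering | P, ICC 0.05 |
|---|---|---|---|---|---|
| 0 | any | 0 | 0% | 5.0% | 5.0% |
| 0.05 | 0.5 | 0.025 | 5% | 5.2% | 5.1% |
| 0.10 | 0.5 | 0.05 | 10% | 5.7% | 5.5% |
| 0.10 | 1.0 | 0.10 | 20% | 7.9% | 7.0% |
| 0.20 | 1.0 | 0.20 | 40% | 17.0% | 13.2% |

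Worked example, last row: bias/SE = 0.20/0.20 = 1.00, so P = Φ(−0.96) + Φ(−2.96) = 0.1685 + 0.0015 = 0.170.

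The first row covers equal AI use in both arms and a supervised test.

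**The case against.** The strongest reply is that the article never says the test is unsupervised. An online form can be filled in during class, direct assessments are mentioned, t1 comes after training, and unlimited exercise use is tied to designated training periods. Test-room details often sit in a fuller protocol or manual. Controls can open a public chatbot as easily as anyone, so the difference between arms is assumed. The example answers are offered for comparison with the student's own exercise responses, not as a service for outside questions. No passage says the test is graded, so the incentive to cheat may be small.

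Much of this stands. A reader might infer that the test is an unsupervised online survey, that HAWKI is open while it is taken, and that the result therefore favours AI. The documents establish none of these three. A reader might also suspect that AI-arm students rehearse the t0 questions in the tool. The article does not say that the same questions recur, and practice on similar vignettes is the intervention itself.

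The objection does not remove the gap. Collection as described would permit AI-assisted answering, and the condition that makes differential use plausible is created by the design. How the primary test is sat is a design matter that analysis cannot repair afterwards.

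**Conclusion.** The concern holds as an unguarded threat to the primary outcome, not as a demonstrated bias. It rests on an inference (the test appears to be taken online) and on a condition (AI use at t1 is more frequent in the AI arm than among controls). If both hold, the primary difference includes the tool's performance and is inflated in favour of AI. The assumed inputs give 0.025 to 0.20 SD. At 0.20 SD, a trial with no true effect would be significant about 17% of the time, or about 13% with an ICC of 0.05. These inputs are illustrations and do not bound the bias. With equal AI use or a supervised sitting, the differential is near zero. Because the safeguard is cheap and must be in place before data are collected, the plan should be changed.

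**What to change.** In Study outcomes, and in the timeline given in the recruitment section:

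- State that the competence test at t0 and t1 is completed during a seminar session in both arms, with an explicit instruction that no AI tool, HAWKI or public, is used.
- State that the study prompts on Stud.IP are hidden from before the t1 session until t1 data collection ends. This alone does not block HAWKI or public chatbots, so the instruction and the in-class setting are also needed.
- Add one item at t1 in both arms asking whether any AI tool was used to answer.
- Record whether each test was completed in class or remotely.

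Keep the ITT comparison of all randomised students as primary. Repeat it without remote or AI-assisted tests only as a sensitivity analysis, and note that this conditions on a post-randomisation variable.

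The cost is one test slot in each of two sessions, a platform visibility setting and one or two survey fields. The downside is a little lost seminar time and some absent students, who can still answer remotely. If the test is already planned as a supervised sitting without AI, saying so settles most of the point.

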Randomisation for the study will be conducted at the seminar level, with each seminar class being randomised according to the scheme outlined in Fig. 1. The randomisation process will be conducted by an independent party to ensure unbiased allocation, using coin-flip or computer-generated randomisation procedures, to determine to which condition (Condition 1 or Condition 2; Cluster Types A and B, respectively) each class is assigned, while a rule is implemented so that, if a given instructor teaches multiple classes in one semester, the difference in the number of classes assigned to Cluster Type A vs. Cluster Type B does not exceed one. Our main comparison focuses on the randomised arms (Cluster Types A and B). Additional non-randomised comparison classes (Condition 3, Cluster Type C) will be included only if a given seminar cannot be randomised due to scheduling or instructor constraints. These observational data serve as ancillary information but will not be part of the main randomisation-based analysis.

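### The non-randomised TAU classes are to be compared only with the AI arm; the randomised TAU arm is the closer check of the contextual differences they are meant to explore

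*Protocol article*

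**What the plan says.** The Study design section describes Condition 3 (Cluster Type C) in one paragraph. Its students "will attend communication skills seminar with instructions and exercises comparable to those in Condition 2", so Types B and C both receive TAU. The only comparison named for them is with the AI arm: "This Condition will serve as an observational, non-randomised control to compare against condition 1, but not be part of the main analyses".

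The paragraph gives two examples of why a class may end up in Type C: "if certain classes already began instruction before randomisation could take place or if they are run by instructors who cannot accommodate the required arrangement". The section on participants, recruitment and randomisation also mentions scheduling. The purpose is then stated: "Such classes serve as an additional, observational comparator to explore potential baseline or contextual differences". The next sentence gives the remedy: "We will address these differences by adjusting for key covariates (e.g., baseline skill levels) in the analyses".

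The randomisation text keeps these classes apart from the main A versus B comparison: "These observational data serve as ancillary information but will not be part of the main randomisation-based analysis". Footnote a of Table 1 adds that Type C "completes the same measures as the control condition in the randomised Cluster Types". The protocol nowhere names a comparison of Type C with Type B.

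**The concern.** The comparator named does not fit the purpose given. To learn whether the non-randomised classes differ in context, one would hold the teaching constant and compare TAU with TAU. The protocol instead names a comparison in which the teaching and the route into the study both differ. A difference at T1 could come from the AI exercises, from the circumstances that made a class non-randomisable, or from both, and A versus C alone cannot tell these apart.

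The remedy is worded too confidently. The stated reasons for Type C status are properties of the class: when it began, how it was scheduled, who teaches it. Such factors can affect how much students learn between T0 and T1. A student's baseline score does not measure them.

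What is at stake is how an ancillary result is read. A versus C could look larger or smaller than the randomised contrast for reasons unrelated to AI. Meanwhile the more useful question, whether the randomised control classes resemble ordinary TAU classes, has no named analysis.

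**Working it through.** The protocol gives no figure on this point, so there is none to reproduce. The check is which contrast identifies what.

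**Inputs**
- A receives AI plus TAU; B and C receive TAU (Study design).
- C differs from A and B in the reasons for non-randomisation (Study design; randomisation text).
- A, B and C all take the primary-outcome test at T0 and T1, and C completes the same measures as B (Table 1 and footnote a).

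**Step 1: simple additive model.** Write the mean improvement in each group as A = μ + AI, B = μ, C = μ + ctx. Here ctx is the combined effect of timing, scheduling, instructor and selection in Type C classes.
- A − B = AI
- A − C = AI − ctx
- C − B = ctx

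The three are linked by (A − C) = (A − B) + (B − C). With A and C alone, the design matrix has rank 2 for 3 parameters, so AI and ctx cannot be separated. With all three groups the rank is 3 and both are identified under this model.

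**Step 2: illustration.** All effects are assumed, in SD units; the protocol supports no particular size or direction.

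| AI | ctx | A − C | C − B |
|---|---|---|---|
| 0 | −0.2 | 0 + 0.2 = 0.2 | −0.2 |
| 0.3 | −0.2 | 0.3 + 0.2 = 0.5 | −0.2 |
| 0.3 | +0.2 | 0.3 − 0.2 = 0.1 | +0.2 |
| 0.25 | +0.25 | 0.25 − 0.25 = 0 | +0.25 |

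A versus C can show an effect where there is none (row 1) and hide one that exists (row 4).

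**Step 3: what baseline adjustment does.** Split ctx into a part carried by baseline skill and a part acting after T0. Adjusting for the T0 score can remove at most the first part. The second stays in A − C. It also stays in C − B, where it is the quantity of interest.

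**Step 4: limit of C versus B.** Suppose the randomised control classes are themselves shifted by s, through spillover from AI classes or through taking part in the randomised comparison. Then B = μ + s and C − B = ctx − s. With ctx = 0 and s = 0.2, C − B is −0.2, the same as with ctx = −0.2 and s = 0. The protocol leaves room for such a shift: contamination is its reason for randomising classes, one instructor may teach both A and B classes in a semester, and Condition 3 has its own consent form. C versus B is therefore the closer check of context, but not a pure one.

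**The case against.** The strongest defence is that Type C is fenced off. The protocol repeatedly calls it observational, optional or ancillary and keeps it out of the main analysis. That stands, and it limits the point to a small improvement.

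Several stronger readings are tempting, and the document does not support them.

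- **That C versus B is ruled out.** It is unnamed, not excluded. The purpose sentence gives no counterpart group, the section on additional analyses allows further sensitivity analyses, and the measures permit the contrast. A condensed article need not list every ancillary contrast. This one does, however, name a contrast for Type C, and the one it names suits the purpose less well.
- **That A versus C cannot serve the purpose at all.** The purpose includes baseline differences, and these can be seen at T0 in any pairing, before AI exposure. The difficulty lies in the T1 outcome.
- **That the confounder is the instructor.** Instructor constraints are one reason among several. A class excluded for its start date or schedule may share an instructor with an A or B class; the protocol does not say.
- **That A versus C will be presented as support for an AI effect.** Nothing says so. The risk is one of reading, not a stated plan.
- **That C versus B isolates context, so A versus C can tell us nothing more about AI.** Spillover or participation effects in B would enter C − B. A TAU group less exposed to spillover could be informative, though confounded.
- **That the covariate adjustment should go.** Baseline skill is offered only as an example of a covariate, and adjustment is useful for either contrast. Only the claim that it settles the differences is too strong.

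**Conclusion.** The point holds as a minor one. The protocol names only the AI arm as comparator for Type C. At T1 that comparison joins the AI effect to the class-level reasons for non-randomisation, and adjusting for baseline skill cannot fully undo this. Type B is the closer comparator for context, with the same kind of teaching and the same measures.

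The algebra assumes additive effects. The distortion in A versus C then equals the contextual difference with its sign reversed, one for one. Its size is unknown, and the 0.2 SD used above is only an illustration. Reading C − B as context further assumes little spillover or participation effect in B.

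A reader might infer that the trial's main result is compromised. It is not: the randomised A versus B comparison does not use Type C.

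**What to change.** In the Condition 3 paragraph of the Study design section:

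1. Name C versus B, adjusted for baseline, as the planned Type C comparison. Describe it as a check of context and of how representative the randomised control classes are, and note that it may also reflect spillover or trial participation in B.
2. Report any A versus C result only beside C versus B, and not as separate evidence of an AI effect.
3. Keep the covariate adjustment, but say that it can only partly address the differences.

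The cost is a few sentences and one additional descriptive contrast. No new data or instruments are needed. Type C arises only where a seminar cannot be randomised, so the contrast will probably rest on few classes and be imprecise; it should be reported with its confidence interval and not as a test that context is absent.
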